#### Post-intervention questionnaire

The effectiveness of the intervention will be measured by the difference of participants' pre- and post-intervention measurements, controlling for covariates. Therefore, all intake questionnaires will be repeated in the post-intervention phase. Along with these repeated scales, several additional measures will be administered.

Two additional questions will measure participants' attitude toward the videos. The first item will measure whether participants would recommend the video to friends with a similar goal (i.e., “Would you recommend these videos to a friend who also wanted to reduce their non-essential consumption?”). The second item will measure participants' intention to continue watching similar videos online (i.e., “Would you watch similar videos online?”). Participants would be required to indicate their answer on a nine-point scale (0 = not at all to 8 = definitely) for both questions. Lastly, an open-ended question will allow participants to share what they thought was interesting, difficult, or helpful during the one week of intervention.

## Proposed analysis

To test the hypotheses, statistical software including Excel, SPSS, and R will be utilized.

### Consumption reduction—behavior

To examine whether user-generated content will reduce excessive consumption, a multiple regression analysis will be calculated, using condition as an independent variable to predict excessive consumption post-intervention, taking the baseline measurement into account as a covariate, in addition to other controlled variables (e.g., base-line values, demographics). As can be seen in Figure 2, we expect a main effect of point of time for all conditions. In other words, we expect to see consumption behavior decreased post-intervention. Additionally, we expect to see an interaction between point of time and condition, showing a stronger reduction of excessive consumption in the experimental groups following the user-generated content intervention in comparison to the control group.

**Figure 2 F2:**
[figure not shown]
Proposed pattern of results showing reduced consumption within experimental groups.

The strength of the effect is expected to be higher between t0 and t7 than between t0 and t_end_. In other words, we expect a stronger effect during the intervention compared to the post-intervention phase. Condition will be contrast coded to facilitate the interpretation of the interaction (Cohen et al., 2013). This analysis will also be used to examine which aspects of user-generated content affect excessive consumption, comparing self-transcendence to self-enhancement conditions. Although, there is no clear expectation on which content will have a stronger effect, this will be examined through exploratory analyses. Participants' in-take reported motivations, values, involvement, and personal goals to reduce consumption will be considered as control variables in these analyses.

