## Abstract

Excessive consumption is on the rise, as is apparent in growing financial debt and global greenhouse gas emissions. Voluntary simplicity, a lifestyle choice of reduced consumption and sustainable consumer behavior, provides a potential solution for excessive consumers. However, voluntary simplicity is unpopular, difficult to adopt, and under researched. The outlined research project will test a method of promoting voluntary simplicity via user-generated content, thus mimicking an existing social media trend (Minimalism) in an empirical research design. The project will test (a) whether the Minimalism trend could benefit consumers interested in reducing their consumption, and (b) whether self-transcendence (i.e., biospheric) and self-enhancement (i.e., egoistic and hedonic) values and goals have a similar impact in promoting voluntary simplicity. A one-week intervention program will test the efficacy of watching user-generated voluntary simplicity videos in reducing non-essential consumption. Each of the two intervention conditions will present participants with similar tutorial videos on consumption reduction (e.g., decluttering, donating), while priming the relevant values and goals (self-transcendence or self-enhancement). These interventions will be compared to a control condition, involving no user-generated content. Participants will undergo baseline and post-intervention evaluations of: voluntary simplicity attitudes and behaviors, buying and shopping behaviors, values and goals in reducing consumption, and life satisfaction. Experience sampling will monitor affective state during the intervention. We provide a detailed stepwise procedure, materials, and equipment necessary for executing this intervention. The outlined research design is expected to contribute to the limited literature on voluntary simplicity, online behavioral change interventions, and the use of social marketing principles in consumer interventions.

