## Objectives

The project will test whether user-generated content promoting either self-transcendence or self-enhancement values and goals could be effective in reducing excessive consumption, as well as increasing well-being. The effectiveness of the interventions will be tested by measuring their effects on life-satisfaction, intent to adopt voluntary simplicity, and purchasing intent and behavior. The project's main research questions are:
Could user-generated content promoting voluntary simplicity reduce excessive consumption?Are self-enhancement goals as effective in promoting sustainable behavior as self-transcendence goals, in user-generated Minimalism content?

We are also interested in whether exposure to user-generated content promoting voluntary simplicity affects one's well-being. Finally, the relationship between one's intent to reduce consumption and one's consumption behavior might generate meaningful insights.

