### Participant outreach

#### Sample size

Two hundred and fifty English-speaking subjects will be recruited for this study globally, via online methods. The number of participants needed is based on an a priori power analysis using G^*^Power software (*F*-test, ANOVA: Repeated measures, within-between-interaction; 1− β = .80, α = .05, Cohen's f = .10), which revealed that the study would require a total sample size of *N* = 198 (Faul et al., 2007). An additional 52 participants have been added to this estimated sample size to account for an assumed 20% dropout rate.

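### A main question asks whether the two video framings are equally effective, but the plan gives it only an exploratory test for a difference, which cannot support a yes

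*Protocol article*

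**What the plan says.** - **Status of the question.** Under Objectives, "The project's main research questions are" introduces two items. The second is "Are self-enhancement goals as effective in promoting sustainable behavior as self-transcendence goals, in user-generated Minimalism content". The Abstract gives the same aim as (b): whether the two kinds of values and goals "have a similar impact in promoting voluntary simplicity".
- **Analysis.** The only analysis assigned to it is under Proposed analysis, Consumption reduction—behavior, in the text after Figure 2: "This analysis will also be used to examine which aspects of user-generated content affect excessive consumption, comparing self-transcendence to self-enhancement conditions". The analysis meant is the regression of post-intervention consumption on condition with baseline as covariate. On coding: "Condition will be contrast coded to facilitate the interpretation of the interaction". On direction and status: "Although, there is no clear expectation on which content will have a stronger effect, this will be examined through exploratory analyses".
- **Sample size.** The Sample size section uses a repeated-measures ANOVA within-between interaction with 80% power and "α = .05, Cohen's f = .10". This gives N = 198, raised to 250 for an assumed 20% dropout. The number of groups, the number of measurements and the correlation are not stated.

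**The concern.** A question that asks whether one framing is as good as another has equivalence as its affirmative answer. A regression contrast tested against zero can answer no, because the arms differ. It cannot answer yes, because failing to find a difference is not evidence of similarity unless the interval is narrow enough to exclude differences that matter. The article therefore pairs a main question with an analysis of the wrong type.

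It also gives the question two ranks: main in the Objectives, exploratory in the analysis section. The sample size, built on an interaction test for a difference, does not address it.

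At stake is half of the main research questions. If the contrast is not significant, the authors have no stated basis for saying anything about it.

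**Working it through.** **Reproducing N = 198.** Power comes from the noncentral F with λ = f²·N·m/(1−ρ), df1 = (k−1)(m−1) and df2 = (N−k)(m−1), for k groups, m measurements and correlation ρ. These three inputs are not stated, so several sets were tried.
- k = 3, m = 2, ρ = 0.6: λ = 0.01 × 198 × 2/0.4 = 9.9 and power 0.805. N = 198 is returned exactly.
- k = 3, m = 3, ρ = 0.5: power 0.792 at 198.
- k = 2, m = 2, ρ = 0.5: power 0.7997 at 198.

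Other sets also come close, so this does not prove which inputs were used. It does show that ρ of 0.5 to 0.6 fits the stated figure. Dropout: 198/0.8 = 247.5, so 248 against 250 stated, which is consistent.

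**Assumptions for the two-arm contrast.** Allocation 1:1:1, so 198/3 = 66 completers per arm; baseline correlation 0.5 to 0.6; differences in units of the outcome SD; normal approximation.

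**Formulas.**
- SE = √(1−ρ²) × √(2/66), with √(2/66) = 0.174.
- CI half-widths: 1.96 × SE (95%) and 1.645 × SE (90%).
- Power for a true difference d: Φ(d/SE − 1.96).
- Smallest margin with 80% power for two one-sided tests at 0.05 when the true difference is zero: (1.645 + 1.282) × SE.

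| | ρ = 0.6 | ρ = 0.5 | unadjusted |
|---|---|---|---|
| SE (SD units) | 0.139 | 0.151 | 0.174 |
| 95% CI half-width | 0.27 | 0.30 | 0.34 |
| 90% CI half-width | 0.23 | 0.25 | 0.29 |
| Non-significant if true d = 0.25 | 57% | 62% | 70% |
| Equivalence margin at 80% power | 0.41 | 0.44 | 0.51 |

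For example, at ρ = 0.6 and d = 0.25: 0.25/0.139 − 1.96 ≈ −0.16, so power is about 0.43 and non-significance about 57%.

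**Scale of these margins.** Take three groups and two times, with both video arms shifted equally against control at the second time only. The group pattern (0, 1, 1) has variance 2/9 = 0.2222 and the time pattern (0, 1) has variance 0.25. Then f = .10 implies δ = 0.10/√(0.2222 × 0.25) = 0.424 SD. The margin that the trial can support is therefore about as wide as the whole planned effect against control.

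**A tighter margin.** Half the planned effect is about 0.21 SD. The 90% half-width of 0.23 to 0.25 SD exceeds it, so equivalence could not be concluded even at an observed difference of exactly zero. With baseline adjustment at ρ = 0.5, 80% power would need 322 per arm for a 0.2 SD margin and 143 per arm for 0.3 SD.

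**Sensitivity.** At ρ = 0.7 the SE is 0.714 × 0.174 = 0.124, the 95% half-width 0.24 and the margin 2.927 × 0.124 = 0.36 SD. With no dropout (83 per arm) and ρ = 0.5, the margin is 2.927 × 0.866 × √(2/83) = 0.39 SD. The picture changes little.

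**The case against.** The strongest reply is that the article makes no equivalence claim. It labels the comparison exploratory, states no directional expectation, and predicts no equality between the video arms under Anticipated results. A margin and an interpretation rule are also details that a condensed article may leave to a full protocol or SAP.

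Much of this stands. A missing margin alone would not be a finding. Three stronger readings are tempting, and the documents do not support them:

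- **That a non-significant contrast will be reported as equality.** No section says so. The remark that null results will be informative concerns whether the videos work at all, and the plan to offer effective interventions to participants afterwards rests on comparison with control.
- **That the article argues for self-enhancement goals in place of biospheric ones.** It says only that they might be used, and that their relative effectiveness is unclear.
- **That a clearly worse arm would probably be missed.** With a shortfall of the full 0.424 SD, power is Φ(0.424/0.139 − 1.96) ≈ 86% at ρ = 0.6 and about 80% at ρ = 0.5. Only differences below about 0.27 to 0.30 SD are more likely missed than found.

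The exploratory label does not remove the mismatch. The Abstract and Objectives still promise an answer on similarity, the analysis that the article fixes cannot give an affirmative one, and a margin set elsewhere would not change the precision available at this sample size.

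**Conclusion.** The concern holds as a mismatch between question and method. The Abstract and Objectives pose an equivalence-type question as a main one, the analysis section meets it with an exploratory difference contrast, and the sample size is for a difference test. That contrast can establish that the arms differ but cannot support equal effectiveness. It would be an inference, not something the article states, that a null will be taken as equality; the article simply gives no other route to that answer.

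Under the assumptions above, the trial can support equivalence only within margins about as large as the planned effect against control. Moderate true differences, around 0.25 SD, would more often than not go undetected.

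This should be fixed but does not threaten the trial: the comparison of videos with control is unaffected.

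**What to change.** Either of two changes resolves it.

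1. **Keep the question and give it a matching analysis.** In the text after Figure 2, commit to reporting the self-transcendence minus self-enhancement difference with its 90% and 95% CI. State that a non-significant contrast will not be taken to mean equal effectiveness, and that this conclusion is allowed only if the 90% CI lies inside a margin justified and fixed before the data are seen. Add that, under the stated assumptions, margins below about 0.4 SD are not powered at N = 198 and a margin near 0.21 SD is unattainable.
2. **Reword the question.** In the Abstract and Objectives, present the comparison of framings as exploratory estimation of the difference, so that it agrees with the analysis section.

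Both are changes of wording only. The cost is that the comparison will probably be reported as inconclusive. Answering the equivalence question at a tighter margin would need a larger trial.

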### Consumption reduction-intent

A similar regression analysis will be calculated exploring the interventions' effects on reported intent to reduce consumption. Consumption reduction intent is expected to increase, especially for participants taking part in the interventions, showing both a main effect of point of time during the experiment, and an interaction effect between point of time and condition.

Furthermore, a correlational analysis, examining the link between the intent to reduce consumption and reported behavior, will be performed. Pearson's correlation coefficient will be calculated between reported behavior and reported intent, controlling for reported commitment to the study. We expect to find a negative link between consumption reduction-intent and consumption behavior.

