## Procedure

At baseline, all participants will download a free mobile application. Participants will complete an intake survey on Qualtrics, through a link in the mobile application. Following intake, participants will be randomly allocated to one of the three experimental conditions, and complete a battery of questionnaires measuring dependent and independent variables (see t0 in Figure 1). After baseline measurements, the intervention will commence. In the two intervention conditions, participants will watch one video daily for 6 days. Both intervention and control condition participants will complete a daily mood measurement (see t1 through t6 in Figure 1). On the last day of the intervention, participants will complete questionnaires measuring the dependent and independent variables a second time (see t7 in Figure 1). One month after intervention completion, the dependent variables will be measured again (see t_end_ in Figure 1).

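### The intent-behaviour correlation controls for commitment but not for condition, so arm effects would bias a post-intervention coefficient, modestly, toward the predicted negative sign

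*Protocol article*

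**What the plan says.** The Objectives section of the protocol article adds, after the two main research questions, that "the relationship between one's intent to reduce consumption and one's consumption behavior might generate meaningful insights". The Consumption reduction-intent section turns this into an analysis: "Pearson's correlation coefficient will be calculated between reported behavior and reported intent, controlling for reported commitment to the study". It also gives the predicted sign: "We expect to find a negative link between consumption reduction-intent and consumption behavior".

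Commitment is the only control named. The section does not say whether the three arms are pooled, which time point is used, or whether levels or changes are correlated. The Design section does say that pre-to-post differences are the dependent variables.

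The plan predicts an arm effect on each of the two variables:

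- Intent: "Consumption reduction intent is expected to increase, especially for participants taking part in the interventions".
- Behaviour: the plan foresees an interaction "showing a stronger reduction of excessive consumption in the experimental groups following the user-generated content intervention in comparison to the control group".

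In the regression models (Consumption reduction—behavior), condition is the independent variable and is to be contrast coded. The correlation is the analysis in which it does not appear.

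**The concern.** The Objectives ask about a person's own intent and own consumption. If both predicted video effects occur, video participants as a group sit higher on intent and lower on consumption than controls. A correlation taken over everyone then picks up this difference between arms as well as any association between individuals. The contribution is negative, which is the sign the plan predicts, and it grows as the videos work better. Controlling for commitment does not remove it unless commitment happens to carry the arm difference.

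What is at stake is the interpretation of one secondary result. A significant negative coefficient could be reported as evidence that intent and behaviour go together when part of it restates two treatment effects.

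**Working it through.** **Inputs from the protocol article.** Three arms, two of them with videos: "participants will be randomly allocated to one of the three experimental conditions" (Procedure). Planning values: power 0.80, "α = .05, Cohen's f = .10" for a repeated-measures within-between interaction, "which revealed that the study would require a total sample size of *N* = 198", and 250 recruited (Sample size). No effect size is given for intent or for behaviour separately, and none for the correlation.

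**Assumptions.** Allocation 1:1:1 (the ratio is not stated), so a share p = 2/3 receives videos and p(1-p) = 2/9. Both video arms shift equally. Within-arm SD is 1, within-arm correlation is zero, and commitment is unrelated to arm.

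**The plan's own figure.** With noncentrality f²·N·m/(1-ρ), k = 3 groups, m = 3 measurements and an assumed ρ = 0.5, the required N is 202, and power at 198 is 0.792. This is close to the stated 198. Dropout: 198/0.80 = 247.5, so 248 against 250 recruited. The sample size therefore serves as a fair basis for N.

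**Step 1: from f = .10 to a video-control shift d.**

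- Read as a three-group f at post-test: f = √(2/9)·d, so d = 0.10/0.471 = 0.21.
- Read as the interaction f: f² = (2/9)·var(time pattern)·d². A pattern (0, 1) has variance 1/4 and gives d = 0.42. A pattern (0, 1, 1) has variance 2/9 and gives d = 0.45.

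**Step 2: the correlation produced by the arms alone.** With a shift of +d on intent and -d on consumption,

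r = -(2/9)d² / (1 + (2/9)d²).

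**Step 3: the rejection rate.** With one control, z = |atanh r|·√(N-4), and the two-sided rate is Φ(z-1.96) + Φ(-z-1.96). Example for d = 0.424 and N = 198: r = -0.0400/1.0400 = -0.038; z = 0.0384 × 13.93 = 0.535; rate = 0.077 + 0.006 = 0.083.

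| d on both variables | induced r | rejection, N = 198 | rejection, N = 250 |
|---|---|---|---|
| 0.20 | -0.009 | 5.2% | 5.2% |
| 0.21 | -0.010 | 5.2% | 5.3% |
| 0.30 | -0.020 | 5.9% | 6.1% |
| 0.42 | -0.038 | 8.3% | 9.3% |
| 0.50 | -0.053 | 11% | 13% |
| 0.80 | -0.125 | 41% | 50% |

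At d = 0.45 and N = 198 the rate is about 9%. Nearly all the excess lies on the predicted side: at d = 0.42, significance with a negative sign occurs in 7.7% of trials against a nominal 2.5%.

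**Step 4: how large a shift would matter by itself.** The critical |r| at N = 198 is 0.140. The induced r reaches it when (2/9)d² = 0.14/0.86, that is d = 0.86 on both variables.

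**Step 5: with condition added.** In simulation (4,000 trials per setting, N = 198) the partial correlation given commitment and condition rejects in 4.5% to 5.7% of trials for every d from 0.2 to 1.0.

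**Effect on the estimate.** With a true within-arm correlation of -0.20 and d = 0.45, the pooled coefficient is (-0.20 - 0.045)/1.045 = -0.23. The condition-adjusted one is -0.20.

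**The case against.** The strongest reply has four parts.

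- **Pooling and time point are not stated.** This is correct, and a baseline-only correlation would carry no arm effect. But the Design section makes pre-post differences the dependent variables, nothing points to a baseline-only analysis, and the section does list a control, which is not condition. The point is therefore conditional on the natural reading, and it is more than a detail left to a fuller plan.
- **A sample-wide correlation is a legitimate description.** If the videos change behaviour through intent, part of the between-arm covariance is a real intent-behaviour link. This stands in part: not all of the induced correlation is artefact. The pooled coefficient, however, cannot separate that case from two unrelated video effects.
- **The effect is small.** This stands. With unequal shifts it is smaller still: 0.42 SD on one variable and 0.2 on the other gives about 6% rejection. A reader might infer inflation of about 2.5 times nominal. That needs d = 0.52 (about 12% rejection), which follows only if exactly half the effect is assumed to remain at one month. The article says the effect will be weaker by then but gives no fraction, and under the same assumption the one-month shift is 0.26 SD with 5.5% rejection.
- **The stakes are low.** This stands too. The correlation is not one of the two main research questions, and treatment effects come from regressions that contain condition.

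**Conclusion.** The point holds as a minor one. The named control set omits the randomised factor while the plan predicts opposite arm effects on the two correlated variables, so a post-intervention or change-score correlation across arms is biased toward the predicted sign. At the planned f = .10 the induced r is about -0.01 to -0.04, and two-sided rejection at N = 198 is about 5% to 9%. This rests on 1:1:1 allocation, equal shifts on both variables and commitment unrelated to arm. The bias is negligible near 0.2 SD and serious only well above 0.5 SD on both variables.

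A reader might go further and infer that the analysis would manufacture the predicted negative link by itself. The documents do not support that: it would take shifts of about 0.86 SD on both variables for the induced r even to reach the significance threshold, and no effect of that size is planned. Nor is any conclusion about the efficacy of the videos affected.

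**What to change.** In the Consumption reduction-intent section:

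1. State which time point, or which change score, enters the correlation.
2. Add condition to commitment as a control, using the two contrast codes already foreseen for the regressions.
3. Report the within-arm correlations alongside.
4. Base the intent-behaviour conclusion on the condition-adjusted coefficient.

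This is a sentence or two of text and needs no new data, since allocation is recorded. It uses two degrees of freedom (195 to 193 at N = 198). In a simulation with a true correlation of -0.20 and no video effect, power fell only from 81.1% to 80.7%.
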